## Conceptualization

Literature has shown that drivers of maternal and child healthcare include characteristics such as; maternal age, gestational age, parity, educational level, wealth index or income, multiple pregnancies, and area of residence [10, 38–40]. These factors are thought to significantly influence the uptake of antenatal care and skilled delivery [41–43]. The overall effect of the factors are moderating and have direct or indirect links to undesirable perinatal outcomes.

Institutional level factors also exist, often at the point of service delivery, and tacitly restrict the full realization of healthcare objectives. They impede policy implementation and influence outcomes of health policy interventions. For example, factors such as staff competence, health facility location, and quality of care are critical to the attainment of the primary outcomes of interest and also play roles to influence the undesirable outcomes.

This study attempts to draw lessons from the Street-Level Bureaucratic theory, as propounded by Lipsky, to examine how service providers, the lower level employee negotiate with policy users to partner government in the implementation of the FMHCP for optimum effect.

Lipsky opined that in policy implementation, the lower level employee is faced with challenges and exercises discretions. He maintained that the employee is the last link to policy formulation and should not be left out in developing workable policies [44, 45] and that, the lower-level employee which he termed the Street-Level Bureaucrat, is the one with the actual implementation role of public policy [48, 46].

The ‘free’ maternal health care policy in practice exercises causal effects through policy effectiveness, and therefore undesirable effects if challenges are present. Thus, this current study proposes a framework (Fig. 1) of quantitative and qualitative design to examine the FMHCP quantum contribution towards maternal healthcare utilization and its effects in combating perinatal deaths.

**Fig. 1 Fig1:**
[figure not shown]
Conceptual framework showing causal relationship between actors and outcome

Also, the study examines the policy, as being implemented, adopting Lipsky’s idea of street-level bureaucracy to addressing a critical question; to what extent does the lower level employee influences the successes of the ‘free’ maternal health care policy in Ghana against the backdrop of funding constraints and implementation challenges.

## Methodological literature

Studies on perinatal health care outcomes in Ghana are scanty and restricted. Existing studies often bothered on stillbirths reported within districts and institutions [20, 21, 45]. Despite the contributions of earlier studies to literature, their findings are limited in scope and do not allow for conclusion relative to in-country strides towards the achievement of the sustainable development goal 3.

The limited research on policy impact on neonatal death highlights the challenges of inadequate research in Ghana context. Of critical importance to policy, continuity is the need to assess policy gains overtime after policy implementation [48, 46].

The one hunch of the ‘free’ policy in its prospect, was to bridge the financial gap to maternal healthcare access and create a situation of increased utilization in maternal healthcare. Nevertheless, copious literature exists to suggest that service providers are rather owed huge sums of monies, a situation which leads to service provider ineffectiveness due to acute shortages of supplies and consumables [43, 47, 51].

This current study aims to measure the impact of the ‘free’ maternal healthcare policy; firstly, on maternal healthcare utilization and secondly, on the effect of facility utilization on stillbirth, perinatal death, and neonatal mortality.

Specifically, the study adopts quasi-experimental methods of propensity score matching technique and difference-in-differences analysis to determine the ‘free’ policy contributions towards the uptake of antenatal care and facility delivery utilization, and its impact in reducing stillbirth, perinatal deaths, and neonatal mortality.

As a novelty, this study also collects qualitative data in an intrinsic case study style, using in-depth interviews and focus group discussions (FGD) to explain the context within which the so-called ‘free’ policy operates.

Impact evaluation design is broadly categorized into two; prospective evaluation design and retrospective evaluation design. The former is designed during the program design stage and incorporated into the implementation plan, in which case, baseline data is collected at the pre-implementation stage using pre-defined variables of interest. Treatment assignment in prospective designs has the advantage of randomization, which is the gold standard.

However, not all programs have the benefits of randomization, particularly, public health programs which are usually targeting populations such as poor communities and vulnerable groups. In these situations, it becomes crucial to adopt quasi-experimental design techniques in evaluating the program in the absence of randomization [49–58]. This is referred to as retrospective design, and is the method of choice for this study, giving the social policy status of the ‘free’ maternal health care policy.

Retrospective design is usually the option available when impact evaluation was not envisaged and incorporated in a public program at the design stage, and in this case, statistical techniques are used to generate the propensity score of treated and untreated units’ characteristics for comparison to determine the treatment difference [49, 51, 52].

## The free maternal healthcare policy in Ghana

The FMHCP was introduced in Ghana through a political declaration in July 2008 by the government of Ghana, with no prior policy framework. Thus, the Ministry of Health (MOH) was tasked to ensure the successful implementation of the policy through the NHIS, an agency under the MOH. In principle, the MOH was tasked to enable the free registration of clinically confirmed pregnant women to access care from NHIS accredited facilities without paying out of pocket.

The policy had no sustainable funding source at the time but relied on an initial £42.5 million ($54.2 million) pledge from the UK government [53]. No clear cut eligibility criteria existed. One needed to be confirmed pregnant by a registered nurse, midwife, or doctor to be enrolled in the national health insurance scheme (NHIS) in the nearest office.

Between 2008 and 2014, the police had registered around 3 million women who benefited from comprehensive maternal healthcare in Ghana at no cost to them, but to the NHIS [28, 54]. With no premium payment, the NHIS appears short-circuited in terms of funding and perhaps, would have to rely on other sources, conventional or otherwise, to fund the ‘free’ policy.

Unsurprisingly, the insurance scheme has since reported funding deficit since the policy implementation characterized by erratic payment of service provider claims, which is copiously documented [47, 55–57]. The slow pace of reimbursement coupled with NHIS card issuance difficulties has created a situation of uncertainty surrounding the implementation of the ‘free’ policy [58].

It is in this light that, this study will seek to explore the current situation of the policy implementation by collecting in-depth primary data from the field of implementation i.e. hospital, clinic, and the policy users to situate the discussions of this study into proper context. Figure 2 presents the number of pregnant women beneficiaries of the policy, while Table 1, below show the proportional changes over the years, indicating inconsistencies in the trend.

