## Hypothesis

This study hypothesis that;H_0_:There is no significant association between antenatal care uptake and the free maternal health care policy.H_0_:There is no significant association between facility delivery utilization and perinatal deaths among women who received the free maternal healthcare policy.H_0_**:**Facility delivery utilization has no significant treatment effect on perinatal deaths among women who received the free maternal health care policy.

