## Operational definitions

*Utilization*: The use of maternal healthcare services rendered in a healthcare facility at any level.

*Maternal healthcare*: Antenatal care clinics and facility delivery services provided to pregnant women in a healthcare facility.

*Antenatal care uptake*: This refers to a 4+ antenatal care visit, thus, antenatal clinic visits of less than 4 are equal to zero visits (or 'no visit').

*Facility delivery*: This is when a pregnant woman gives birth in a healthcare facility at any level.

*Stillbirth*: This refers to the birth of a fetus with no signs of life, after 28 weeks of gestation or the death of a fetus within 24 h after birth.

*Perinatal death*: This refers to the number of stillbirth plus the death of neonates within the first week of life.

*Neonatal deaths*: This refers to the number of newborn deaths within 28 days of life.

*Treatment group*: Pregnant women study participants registered with the national health insurance scheme and made 4+ antenatal care visits or pregnant women participants in Ghana who delivered in a healthcare facility.

*Comparison group*: Pregnant women study participants registered with the national health insurance but have made less than 4 antenatal care visits with less than four minimum antenatal visits or pregnant women who did not deliver in a healthcare facility within the study period.

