### Variables of interest

The maternal healthcare utilization examines two primary outcome variables which include; antenatal care up-take (4+ visit = 1, and ≤ 3 visits = 0), and facility delivery utilization, also binary outcome (facility delivery = 1 and home delivery = 0). Mothers’ health insurance status (proxy to the FMHCP) is the exposure variable of interest in this study.

Stillbirth, perinatal death, and neonatal mortality are secondary outcome variables of interest generated as binary outcomes from the DHS data sets using variable *b6,* and *b7* against which the policy utilization impact will be measured. Table 5 presents the derived variables generated using STATA 15.0 from the 2008/2014 DHS data sets.

**Table 5 Tab5:** Variables of interest

Item	Label	Name	Recoding	Binary V
1	Respondent holds valid NHIS card	*S1015*	Holds a valid NHIS card (with or with no evidence) = 1 No valid NHIS card = 0	*Vid_1*
2	Respondent hold valid NHIS card	*S1015*	Holds a valid NHIS card (with evidence) = 1 No valid NHIS card plus (holds a valid NHIS card with no evidence) = 0	*Vid_2*
3	Number of ANC visit during pregnancy	*m14*	Antenatal visits 0–3 = 0 Antenatal visits ≥ 4 = 1	*anc4*
4		*m15*	Home delivery = 0 All facility delivery = 1	*fdelivery*
5	Age at death	*b6*	Alive after day 0 = 0 Born dead/died on day 0 = 1	*stillbirth*
6	Age at death	*b6*	Did not die before 7th day = 0 Died before 7th day of life = 1	*prdeaths*
7	Age at death (months imputed)	*b7*	Did not die before 28th day = 0 Died before 28th day of life = 1	*neodeaths*

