### Covariates

Covariates are the moderating factors identified in the study conceptual framework. Covariates that show significant association with the variables of interest under consideration will be controlled for using multiple logistic regression. These include maternal characteristics such as; age, parity, pregnancy status, cesarean section, educational status, twin pregnancy, income level, abortion, and marital status. These will be adjusted for as confounding using logistics regression models. Population characteristics such as wealth index, distance, region, educational status, and rural/urban residence will also be adjusted for as confounding variables [42].

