### Data analysis

The secondary data will be cleaned and organized, dropping irrelevant variables and renaming covariates for ease of reference as necessary. Essentially, variables of interest in this study are binary outcomes i.e. 1 = case/the presents of an intervention, and 0 = no case, the absence of intervention, control.

Both multivariate logistic regression and Poisson with robust standard error, or negative binomial regression depending on whether there is over dispersion (conditional variance exceeding the conditional mean) will be fitted and analyzed. Thus, **loge** {*p*1 / *(1—pi)*} = *b0* + *b1 Xi1* + *b2 Xi2* + … + *bkXik*. The Use of the multiple logistic regression model also comes with the advantage of adjusting for confounding by including the covariates in the model.

For the matching method, Ghana’s DHS data sets (2008 and 2014) will be merged. This will increase the sample size to n = 8876, and add power to the study. The merger will also eliminate the risk of lack of common support, the so-called curse of dimensionality, a common phenomenon in propensity score matching, where treated units propensity scores cannot find suitable pairs.

Descriptive data will be presented using tables, frequencies, and proportions. The data will then be analyzed distinctly, using multiple statistical models and quasi-experimental design techniques. Firstly, the student independent *t*-test will be used to test for proportions, the significance of association, and mean differences between the independent variable, and the binary outcomes of interest; antenatal care uptake, and facility delivery utilization.

Test of association set < 0.05 less of significance, between the secondary variables of interest (stillbirth, perinatal death, and neonatal mortality) and the covariates; mothers age, marital status, level of education, wealth index, region, area of residence, twin delivery, parity, and employment status will be determined by using the Rao Scot Chis-square, which has an added sensitivity advantage, while adjusting for complex survey design features (weighting, clustering and stratification).

Only covariates found to be significantly associated with the dependent or independent variables will then be included in a multiple logistic regression model and adjusted for confounding [72].

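### Card status can follow from the care-seeking that ANC4+ counts, so the card-versus-ANC4+ comparison is an association and not evidence of a policy effect

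*Protocol article*

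**What the plan says.** **Route into the policy.** The section The free maternal healthcare policy in Ghana describes "free registration of clinically confirmed pregnant women to access care from NHIS accredited facilities", and states: "One needed to be confirmed pregnant by a registered nurse, midwife, or doctor to be enrolled". Contact with a health worker comes first and registration follows, at the nearest scheme office.

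**Exposure.** Variables of interest states that the mother's "health insurance status (proxy to the FMHCP) is the exposure variable of interest in this study". Table 5 takes it from the item "Respondent holds valid NHIS card" (S1015), coded yes/no in two versions that differ only in whether the card was seen. Neither route nor date of enrolment is coded.

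**Outcome and test.** ANC4+ is 1 for four or more visits (m14) and 0 for none to three. Operational definitions adds that "antenatal clinic visits of less than 4 are equal to zero visits". The first null hypothesis is "There is no significant association between antenatal care uptake and the free maternal health care policy". Data analysis plans a t-test of "the significance of association, and mean differences between the independent variable, and the binary outcomes of interest", then regression.

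**Adjustment.** Covariates lists "age, parity, pregnancy status, cesarean section, educational status, twin pregnancy, income level, abortion, and marital status", plus wealth, distance, region, education and residence.

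**Reading of the result.** Expected outcome anticipates significant associations for the primary outcomes and attributes them to the policy.

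**The concern.** The exposure lies partly downstream of the behaviour that the outcome counts. A woman with no health-worker contact cannot get a card through the policy route, and if she made no antenatal visit she also scores 0 on ANC4+. Women who do make contact may or may not hold a card. The uncarded group is therefore enriched with women who never attended, and attendance can produce the card without the card changing attendance.

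Wealth, distance and residence are correlates of care-seeking, but none of them records whether or when contact occurred. The enrolment rule ties card to contact within every level of those covariates, so adjustment does not break the link. Statistical assumptions supposes no unobserved systematic differences for the matching, and Scope and limitations names only the lack of randomization.

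What is at stake is Objective 1. A positive card-ANC4+ result could be reported as a policy success when the enrolment rule alone would produce it, and the bias runs in the policy's favour.

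**Working it through.** **The plan's own figure.** The article gives no card rate, ANC4+ rate or never-attender share. Its only related figure is the merged Ghana sample, 2992 + 5884 = 8876, which reproduces. All rates below are assumptions.

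**Step 1: a model with no policy effect.** Let z be the share of women with no contact, a = 0.80 the ANC4+ share among attenders whatever their card, c the share of attenders who gain a policy card (among those without another card), and g the share holding a card by a route that needs no contact. Write k = g + (1-g)c for the card share among attenders. Then

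- with card: p1 = a(1-z)k / [(1-z)k + zg]
- without card: p0 = a(1-z)(1-c) / [(1-z)(1-c) + z], because (1-g) cancels.

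With g = 0, p1 = 80%. For z = 2% and c = 0.4, p0 = 0.80 × 0.588 / 0.608 = 77.4%.

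| z | p0 at c = 0.4 | p0 at c = 0.6 | False difference (points) |
|---|---|---|---|
| 2% | 77.4% | 76.1% | 2.6 to 3.9 |
| 5% | 73.5% | 70.7% | 6.5 to 9.3 |
| 10% | 67.5% | 62.6% | 12.5 to 17.4 |

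If every woman makes contact (z = 0), the difference is zero.

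**Step 2: dilution by ordinary membership.** Take c = 0.5 and g = 0.4, so k = 0.4 + 0.6 × 0.5 = 0.70. At z = 10%, p1 = 0.504 / 0.67 = 0.752 and p0 = 0.36 / 0.55 = 0.655, a difference of 9.8 points against 14.5 with g = 0.

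**Step 3: chance of a significant result when there is no effect.** The 2014 Ghana sample is 5884. Assume a design effect of 2 (effective n = 2942), a two-sided test at 0.05, and that every record contributes an antenatal count. At z = 2%, c = 0.5, g = 0 the groups are about 1442 and 1500 and the difference is 0.0314. The standard error is √(0.80 × 0.20/1442 + 0.7686 × 0.2314/1500) = 0.01515, the ratio is 2.07, and the rejection probability is 0.54.

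| z | Points, g = 0 | P(significant) | Points, g = 0.4 | P(significant) |
|---|---|---|---|---|
| 2% | 3.1 | 0.54 | 2.2 | 0.27 |
| 5% | 7.6 | 0.998 | 5.3 | 0.87 |
| 10% | 14.5 | 1.00 | 9.8 | 1.00 |

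**Step 4: does restricting to m14 ≥ 1 repair it?** In the Step 1 model it does, because enrolment there depends only on having any contact. Now suppose instead that each visit is a chance to enrol: visits are Poisson with mean 4.5, the enrolment chance is 0.1 per visit, g = 0, and the card again has no effect.

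- Women without a card have Poisson(4.05) visits: p0 = 1 - e^(-4.05)(1 + 4.05 + 8.20 + 11.07) = 0.5762.
- All women: 1 - e^(-4.5)(1 + 4.5 + 10.125 + 15.1875) = 0.6577. The uncarded share is e^(-0.45) = 0.6376.
- Women with a card: p1 = (0.6577 - 0.6376 × 0.5762) / 0.3624 = 0.801. The difference is 0.225.
- Restricted to at least one visit: p0 = 0.5762 / (1 - e^(-4.05)) = 0.586. The difference is 0.215.

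The restriction removes almost nothing here. Over means of 4.5 to 5.5 visits, enrolment chances of 0.1 to 0.4 and g of 0 to 0.3, the unrestricted false difference runs from 0.12 to 0.45, although about 99% or more of women have some contact.

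**The case against.** **The card is not the policy.** S1015 records any valid NHIS card. A reader might infer that insured women as a whole are pre-selected attenders and that never-attenders are always uncarded. The documents do not support that, because the link is strict only for cards gained through the policy route. This stands; Step 2 shows that ordinary membership dilutes the bias without removing it.

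**Confirmation is not an antenatal visit.** The article does not say that the confirming contact is counted in m14, it describes eligibility as lacking clear criteria, and one contact is well short of four. This also stands. If contact is near universal and enrolment happens only at first contact, the bias is small.

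**Rejection is not certain.** A reader might infer that the null will be rejected in any survey of this size. Step 3 does not bear that out: at 2% never-attenders the probability is 0.27 to 0.54.

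**The plan already has a contrast free of this problem.** Data analysis uses difference-in-differences to determine policy impact, and both Objective 1 and the first hypothesis speak of association. It would be wrong to extend the concern to the Ghana-Kenya contrast, or to the 2014-versus-2008 matching in Study design, since neither is defined by card holding. But the plan does not confine the policy claim to them. Variables of interest names the card as proxy for the policy, Data analysis also derives policy impact from matching, for which Operational definitions gives a registration-based group definition, and Expected outcome attributes the primary associations to the policy.

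**Conclusion.** The concern holds for card-based analyses: the t-test, the regression, and any matching on card status. Because confirmation of pregnancy precedes free enrolment and no covariate captures care-seeking, these can show a positive association with ANC4+ when the policy has no effect. Under the assumed rates (80% ANC4+ among attenders, 40-60% of attenders carded, no cards among never-attenders) the false difference is about 3 to 17 points for 2-10% never-attenders. It is smaller where never-attenders hold cards, and could be larger if women enrol at later visits. The documents fix none of these rates, so the direction is better established than the size. Merging 0 with 1-3 visits does not cause the bias, but it hides the pattern that would reveal it.

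**What to change.** - In Variables of interest, Data analysis and Expected outcome, state that the policy effect on antenatal uptake is taken from the country-by-round difference-in-differences. State that the card-versus-ANC4+ result is reported as an association only, and drop its attribution to the policy.
- Add a table of 0, 1-3 and 4+ visits by card status, from m14 and S1015.
- If the comparison among women with m14 ≥ 1 is shown, label it a sensitivity analysis. It fails when women can enrol at later visits, and it conditions on a variable that the policy may itself affect.

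The cost is one table from variables already in Table 5 and a few sentences. The downside is that the card analysis no longer supports a causal claim by itself.

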**Fig. 2 Fig2:**
[figure not shown]
Trend of free maternal health care policy enrollment

**Table 1 Tab1:** Registration under the free maternal health care

Year	No. of enrollment	Percentage change
2008/2009	383,216	–
2010	504,609	24%
2011	485,460	− 4%
2012	754,658	36%
2013	774,009	3%
Total	2,901,952	

Source: NHIA Report, 2013

## Operational definitions

*Utilization*: The use of maternal healthcare services rendered in a healthcare facility at any level.

*Maternal healthcare*: Antenatal care clinics and facility delivery services provided to pregnant women in a healthcare facility.

*Antenatal care uptake*: This refers to a 4+ antenatal care visit, thus, antenatal clinic visits of less than 4 are equal to zero visits (or 'no visit').

*Facility delivery*: This is when a pregnant woman gives birth in a healthcare facility at any level.

*Stillbirth*: This refers to the birth of a fetus with no signs of life, after 28 weeks of gestation or the death of a fetus within 24 h after birth.

*Perinatal death*: This refers to the number of stillbirth plus the death of neonates within the first week of life.

*Neonatal deaths*: This refers to the number of newborn deaths within 28 days of life.

*Treatment group*: Pregnant women study participants registered with the national health insurance scheme and made 4+ antenatal care visits or pregnant women participants in Ghana who delivered in a healthcare facility.

*Comparison group*: Pregnant women study participants registered with the national health insurance but have made less than 4 antenatal care visits with less than four minimum antenatal visits or pregnant women who did not deliver in a healthcare facility within the study period.

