## Specific objectives

To determine any significance in association between the FMHCP and antenatal care uptake, and facility delivery utilization in Ghana.To compare the difference in perinatal outcomes between Ghana and Kenya relative to the ‘free’ maternal health care policy.To measure the treatment effect of facility delivery on stillbirth, perinatal deaths, and neonatal mortality among women who received the FMHCP program compared to those who did not receive the program.To describe the ‘free’ maternal health care policy implementation in its current state in Ghana, within the context of funding constraints and implementation bottlenecks.

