## Methodology

### Study design

This study employs a mixed methodology in two-prongs. The first prong uses two quasi-experimental methods of a difference-in-differences (DID) analysis and propensity score matching (PSM) technique to analyze Demographic and Health Survey data sets of Ghana 2008/2014 and Kenya 2008/2014. Thus, the 2008 data set for the two countries forms the baseline data, while, the 2014 DHS data sets of countries, represents the end line data set.

The DID method necessarily requires comparable data sets from a different country, other than Ghana, that had not implemented the intervention (the 'free' policy) at the time, hence Kenya. The rationale for choosing Kenya is further explained below and will allow for comparison using data from a non-intervention country at the time, but with similar timelines data sets from DHS. This is also necessary for testing the parallel trend assumption applied in DID.

The propensity score matching (PSM) technique will also be used to estimate the average treatment effect on the treated through the generation of the propensity scores of the two groups; the treated group, post-intervention (2014 DHS) and the untreated group, pre-intervention data (2008 DHS) for comparison using the observed characteristics. The study then assumes that the unobserved characteristics are similar and cancels out, applicable in PSM.

The second prong of the study employs an intrinsic care study design to effect, collecting primary data through one-on-one in-depth interviews, and focus group discussion techniques from the Upper East Region of Ghana for analysis. Inductive thematic analysis will guide the management of the qualitative data using INVIVO 12, with vivid quotations to convey participants’ impressions.

The mixed-method design is driven by the overarching goal of the study; first to measure the free maternal healthcare policy effect on maternal healthcare utilization and to determine the impact of the utilization on stillbirth, perinatal death, and neonatal mortality.

Secondly, the study aims to explore an in-depth understanding of the policy in practice under its current operational constraints to explain policy workability from user and service provider perspectives. Figure 3, presents the diagrammatical representation of the study design.

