### Outcome variables

Antenatal care uptake and facility delivery utilization are the primary outcomes of interest. However, on the secondary level of analysis for the FMHCP impact, stillbirth, perinatal death, and neonatal mortality are the secondary outcomes variables, to determine the policy effect.

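### The printed treatment and comparison groups are built from the two primary outcomes, carry no clean policy contrast, and conflict with the exposures named elsewhere

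*Protocol article*

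**What the plan says.** Under Operational definitions, the treatment group is women "registered with the national health insurance scheme and made 4+ antenatal care visits or pregnant women participants in Ghana who delivered in a healthcare facility". The comparison group is women "registered with the national health insurance but have made less than 4 antenatal care visits", "or pregnant women who did not deliver in a healthcare facility within the study period".

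Under Outcome variables, "Antenatal care uptake and facility delivery utilization are the primary outcomes of interest". Variables of interest codes the first as "antenatal care up-take (4+ visit = 1, and ≤ 3 visits = 0" and the second as facility versus home delivery. These are the same splits that define the groups.

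Who counts as exposed is stated differently elsewhere:

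- Variables of interest and Exposure variables: the mother's "health insurance status (proxy to the FMHCP) is the exposure variable of interest in this study".
- Study design, for the propensity score matching: "the treated group, post-intervention (2014 DHS) and the untreated group, pre-intervention data (2008 DHS".
- Statistical methods and rationale, for the difference-in-differences analysis: Ghana versus Kenya, 2008 and 2014.
- Exposure variables, at the secondary level: antenatal uptake and facility delivery are predictors of stillbirth, perinatal death and neonatal death.

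The third specific objective concerns the effect of facility delivery on deaths "among women who received the FMHCP program compared to those who did not receive the program".

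**The concern.** A group label that is meant to carry a policy effect should be fixed without reference to the outcome. Here the label is a function of the two primary outcomes. If an analyst takes the printed definitions and estimates the average treatment effect on the treated for antenatal uptake or facility delivery, the definition determines much or all of the answer.

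The labels also do not separate women who had the policy from women who did not, which is the comparison the third objective asks for. And because each group joins two criteria with an alternative, it is unclear whether the groups are meant to be exclusive. An analyst who follows Operational definitions, one who follows Study design and one who follows Variables of interest would build three different within-Ghana comparisons and report each as the policy effect.

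**Working it through.** The check is one of logic. The only related figure in the plan is the pooled Ghana sample for matching, 2,992 + 5,884 = 8,876, which adds up and is not in dispute.

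**Rules as printed.** Let I = insured, A = 4+ antenatal visits, F = facility delivery. For women in Ghana:

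- Treatment: (I and A) or F
- Comparison: (I and not A) or (not F)

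**All eight kinds of Ghanaian women, with the alternatives pooled:**

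| Insured | 4+ visits | Facility delivery | Treatment | Comparison |
|---|---|---|---|---|
| yes | yes | yes | yes | no |
| yes | yes | no | **yes** | **yes** |
| yes | no | yes | **yes** | **yes** |
| yes | no | no | no | yes |
| no | yes | yes | yes | no |
| no | yes | no | no | yes |
| no | no | yes | yes | no |
| no | no | no | no | yes |

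**Overlap.** Two of the four insured rows meet both definitions: 4+ visits with home delivery, and fewer than 4 visits with facility delivery.

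**Circularity, clause by clause.**

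- Antenatal clause alone: treated are I and A, comparison are I and not A. Antenatal uptake is 100% versus 0%.
- Delivery clause alone: treated are F, comparison are not F. Facility delivery is 100% versus 0%.
- Pooled rule with the two overlapping rows dropped: the three remaining treatment rows all have facility delivery and the three remaining comparison rows have none. Facility delivery is again 100% versus 0%.

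None of these results uses an assumed prevalence, and none changes if the policy had no effect.

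**Policy contrast.** In the antenatal clause both sides are insured, so insurance does not differ. In the delivery clause neither side has an insurance condition; two of the treatment rows are uninsured women.

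**Conflict with other sections.** Under Variables of interest, the two uninsured facility-delivery rows are unexposed; under Operational definitions they are treated. Under Study design, treatment depends only on survey year, so an insured 2008 respondent is untreated and an uninsured 2014 respondent is treated; card status gives the reverse in both cases. Data analysis refers to treated and untreated units for nearest-neighbor matching without saying which rule applies.

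**The case against.** The strongest reply is that the printed groups belong to the secondary level. The third objective opens with the effect of facility delivery on deaths, the second and third research questions and the third hypothesis treat facility delivery in the same way, and Exposure variables makes antenatal uptake and facility delivery predictors at that level. As exposures for deaths they are legitimate. Each alternative can then be read as its own paired contrast: 4+ versus fewer visits among insured women, and facility versus non-facility delivery. On that reading no woman is in both groups.

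Much of this stands. A reader might infer that the study's utilization effect is circular outright. The documents do not support that: no section says the printed groups will be used for the utilization outcomes, and insurance status, survey year and country are all non-circular. A reader might also count Ghana versus Kenya as a further contradiction, but it is simply the difference-in-differences contrast. Nor can a share of women in both groups be given, since the article reports no joint distribution of insurance, visits and place of delivery.

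The reply does not dispose of the point. Operational definitions does not limit the groups to the death outcomes or describe paired contrasts. Methodological literature applies the same two methods to utilization as well as deaths, and Statistical assumptions states the matching assumption using the same group labels. Even on the paired reading the groups compare users with non-users of care, not policy with no policy.

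**Conclusion.** The definitions are wrong as written; this is not detail left to a fuller document.

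Three parts hold without condition: the groups are formed from the primary outcomes at identical cut-offs; the antenatal clause has no policy contrast and the delivery clause admits uninsured women as treated; and the definitions conflict with the exposure in Variables of interest and the matching groups in Study design.

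Two parts are conditional. The 100% versus 0% result arises if these groups are used for the utilization outcomes. The overlap of two insured Ghanaian categories arises if the alternatives are pooled, which is the literal reading. No prevalence assumption enters any of this.

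**What to change.** Replace the two group definitions with mutually exclusive ones for each level of analysis, and delete the alternatives joined by "or" in both.

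- **Level 1, policy to utilization.** Difference-in-differences: Ghana versus Kenya by survey period. Matching: one stated within-Ghana policy exposure that reconciles Study design (survey year) with Variables of interest and Exposure variables (insurance status). Antenatal uptake and facility delivery appear only as outcomes.
- **Level 2, utilization to deaths.** Antenatal uptake (yes/no) and facility delivery (yes/no) as two separate binary exposures, reported as effects of utilization and not as the policy effect.

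Then align Operational definitions, Study design, Variables of interest and Exposure variables. The cost is protocol wording and recoding of group indicators in survey data to which access is already approved; no new data collection is needed.

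The correction does not require matching to be confined to covered versus uncovered women in post-policy Ghana. That would replace the stated pooled 2008/2014 design and bring self-selection into enrollment, so it is a separate design choice.
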